**5. STUDY DESIGN**

This trial is a randomized national multicentre study comparing intensified and conventional follow-up schedule for patients after curative treatment of colorectal cancer. The inclusion is during maximal 2.5 years or until 2000 patients are included. Total expected duration 3 years. Patients may enter during their first three years after curative treatment[[1]](#footnote-2) of colorectal cancer.

The study is constructed with the stepped-wedge design. This implies a randomization at hospital level. The surgeons in a hospital control all their eligible patients according to the care as usual. At the moment determined by the randomization, all included patients will change to the intensified study follow-up protocol. As a result, the early-randomized hospitals have a large amount of patients in the study group and a small amount of patients in the control group, where in the late-randomized hospitals it is the other way around. Randomization will take place on July 1st, 2010 and randomization will be performed per two hospitals. The firstly randomized hospitals start with the intensified follow-up scheme on January 1st, 2011 and since ten hospital will participate, the last two hospitals start with the intensified follow-up scheme at January 1st, 2012.

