**7. TREATMENT PERIODS**

*7.1. Control period*:

Outpatient clinic at 3 months after end of treatment (surgery or adjuvant chemotherapy)

Assessment for fitness to undergo metastasectomy[[2]](#footnote-3)

Care as usual according to the Dutch guidelines ([www.oncoline.nl](http://www.oncoline.nl/)) and local amendment. The actual care as usual given may differ per hospital. Herefore, the standard care as usual per hospital will be described.

Filling out the questionnaire “SF-12 “ after 12 months

*7.2. Intervention period*:

Outpatient clinic at 3 months after end of treatment (surgery or adjuvant chemotherapy)

Assessment for fitness to undergo metastasectomy2

During year 1

CEA measurement every 8 weeksatlocal laboratory, report results by letter. The possibilities for blood sampling at a local laboratory are now examinated per hospital. The measurement will take place at the hospital itself, samples will be mailed to the laboratory.

If no special events occur, no additional out patient clinic visits

At year 1 helical CT-abdomen[[3]](#footnote-4) and colonoscopy[[4]](#footnote-5)

Filling out the questionnaire “SF-12 “ after 12 months

Filling out the questionnaire of intensified follow-up at 1 year

One year after surgery outpatient clinic visit

- Results from evaluation (CT) and evaluation long term surgical results

- Update assessment for fitness metastasectomy

During year 2

CEA measurement every 8 weeks atlocal laboratory, report results by letter

If no special events occur, no additional out patient clinic visits

At year 2 helical CT thorax/abdomen4

Two years after surgery outpatient clinic visit

Results from evaluation (CT) and evaluation long term surgical results

Update assessment for fitness metastasectomy

During year 3

CEA measurement every 12 weeks atlocal laboratory, report results by letter

If no special events occur, no additional out patient clinic visits

At year 3 helical CT thorax/abdomen

Three years after surgery outpatient clinic visit

Results from evaluation (CT) and evaluation long term surgical results

Update assessment for fitness metastasectomy

All patients will be informed about the laboratory results by letter or email. In case of positive results patients will be invited to undergo a CT scan followed by an outpatient clinic visit. All patients will have access to the surgeon’s outpatient clinic in case of questions or clinical complaints.

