## 8. METHODS

## *8.1. Study parameters/endpoints*

### *8.1.1. Main study parameter/endpoint*

Percentage of patients with curative metastasectomy of liver- and lung metastasis from colorectal carcinoma in the study period: July 2010 – October 2012.

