# 10.STATISTICAL ANALYSIS

In the clinical study, the main analysis will be based on the differences between care as usual (pre-treatment) and care after implementation of the CEA watch (post-treatment) regarding the percentage of patients with resected metastases, using a multilevel model to adjust for the clustering. For the quality of life data the same analysis will be applied. In addition, potential confounders such as age, gender and tumour status will be considered.

In an economic evaluation, costs and outcomes of both follow-up strategies will be assessed and compared. Research question in the economic evaluation: “What is the incremental cost-effectiveness of a computer based (CEA-watch) follow-up protocol, compared to follow-up care as usual?” Results of the cost-effectiveness analysis will display the additional costs per additional patient with curative metastasectomy. In addition, a cost-utility analysis will be conducted, based on the quality adjusted life years (QALYs). Both types of analyses will be conducted in order to be able to estimate the balance between costs and effects on health, survival and quality of life. Costs will be studied from a societal perspective, during a time period maximally 3 years. Since the time horizon of the study exceeds one year, both costs and effects beyond the first year will be discounted, using various discounting rates of 3%, 4% and 5%, and no discounting, to facilitate international comparison of study results.

Bootstrapping will be performed on the cost and effect pairs in order to calculate confidence intervals. Cost effectiveness acceptability curves will be constructed to illustrate the probability that the different follow-up strategies will be cost-effective, given different monetary values per additional unit of health (patient with patient with curative metastasectomy/QALY).

Relevant cost components of both follow-up strategies will be assessed for all included patients. Main cost categories will be ultrasound, CT-scan, colonoscopy, CEA assay, ‘CEA watch’ system, additional diagnostic tests, outpatient visits, hospital admissions and travel expenses.

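### One SF-12 per condition at an undefined 12 months, with no baseline or later form, cannot support QALYs over up to three years and leaves only a weak quality-of-life comparison

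*Protocol*

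**What the plan says.** Section 10 makes two commitments that need quality-of-life data.

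- Quality of life is to be compared between conditions with the multilevel model used for the main outcome: "For the quality of life data the same analysis will be applied".
- A cost-utility analysis is added to the cost-effectiveness analysis: "In addition, a cost-utility analysis will be conducted, based on the quality adjusted life years (QALYs"). Its horizon is long: "Costs will be studied from a societal perspective, during a time period maximally 3 years", and "both costs and effects beyond the first year will be discounted". Cost and effect pairs are to be bootstrapped, and acceptability curves drawn per QALY.

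The data come from Section 7. The same line stands under the control period (7.1) and the intervention period (7.2): "Filling out the questionnaire “SF-12 “ after 12 months". No SF-12 is listed at entry or in years 2 and 3, and the starting point of the 12 months is not given. One other form is scheduled, in the intervention period only: "Filling out the questionnaire of intensified follow-up at 1 year".

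Section 5 sets the calendar. Ten hospitals switch two at a time, the first pair on 1 January 2011, and "the last two hospitals start with the intensified follow-up scheme at January 1st, 2012". Section 8.1.1 gives the period for the main parameter: "colorectal carcinoma in the study period: July 2010 – October 2012". Section 6.2 admits new patients and patients operated on up to three years before the start.

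**The concern.** A QALY is the area under a patient's utility curve. With at most one value per condition there is no curve. The value cannot register a recurrence, a metastasectomy or palliative treatment at another time, and no utility is measured after month 12 for the discounting to act on. Bootstrapping cost and effect pairs implies a QALY for each patient, so the gap concerns the trial's own data. An analysis plan written later could not fill it, because the forms would never have been collected.

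The timing is a second difficulty. Patients enter at very different times since surgery and change condition on a calendar date, so a single form at 12 months may fall outside the study or inside only one condition. At stake are a named secondary outcome and the cost per QALY, in a trial that aims at a cost-effective recommendation. Section 10 also puts the travel-expense question on the quality-of-life questionnaire, so that cost item has the same gap.

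**Working it through.** The protocol gives no sample size or precision figure for quality of life or QALYs, so there is none to reproduce. The primary sample size (115, 460, about 800) does not bear on this point.

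**1. What one value supports.** With utilities u at times t, QALY = Σ ½(u_j + u_{j+1})(t_{j+1} − t_j). This needs at least two values, spread over the horizon. With a single u at 12 months, the only route is to hold it constant, QALY = u × survival time. That assumes no change before month 12 and none up to year 3.

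**2. Clock from the start of each period.** Inputs: start 1 July 2010; switches every three months from 1 January 2011 to 1 January 2012 (Section 5 and the summary); end at 1 or 31 October 2012 (Section 8.1.1).

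| Pair | Switch | Control, months | Intervention, months to 1 Oct / 31 Oct 2012 |
|---|---|---|---|
| 1 | 1 Jan 2011 | 6 | 21 / 22 |
| 2 | 1 Apr 2011 | 9 | 18 / 19 |
| 3 | 1 Jul 2011 | 12 | 15 / 16 |
| 4 | 1 Oct 2011 | 15 | 12 / 13 |
| 5 | 1 Jan 2012 | 18 | 9 / 10 |

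- Shorter than 12 months: control of pairs 1 and 2, intervention of pair 5, so 3 of 10 pair-periods.
- Exactly 12 months: control of pair 3, and also intervention of pair 4 if the end is 1 October. Excluding these gives 4 of 10 (end 31 October) or 5 of 10 (end 1 October).
- Both conditions reach 12 months in pairs 3 and 4, so 6 of 10 hospitals cannot supply both. To 31 October, dropping pair 3, whose form falls due on its switch date, makes it 8 of 10. To 1 October with exact 12s excluded, no pair supplies both.
- The summary's timeline (control 3, 6, 9, 12, 15 months; intervention 24, 21, 18, 15, 12) also gives 3 too short, 2 exactly 12, and two pairs with both.

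These counts apply to patients present when the period starts. Later entrants have less time.

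**3. Clock from surgery.** Assumption: constant surgery rate.

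- Patients already in follow-up: surgery 36 to 0 months before the start. Those more than 12 months out have passed the date: (36 − 12)/36 = 67%.
- All patients, study of 28 months, last surgery at month 25 (first visit three months later): surgery dates span 36 + 25 = 61 months. The 12-month date falls inside the study for surgery from month −12 to month +16, which is 28 months. 28/61 = 46% can supply a form and 54% cannot.
- With a 27-month study and surgery up to month 27: 27/63 = 43% can and 57% cannot.

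Each of these patients gives one value, in one condition. Every pair-period keeps some, but unevenly. In a 27-month study the control share rises from 6/42 = 14% in pair 1 to 18/54 = 33% in pair 5, while the intervention share falls from 21/63 = 33% to 9/63 = 14%.

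**4. Clock from each patient's own registration.** Everyone registered in July 2010 reaches month 12 inside the study, whatever the surgery date. Reaching it while still in control is harder: in pair 4 only patients registered in the first 15 − 12 = 3 months do so.

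**The case against.** The defence has real force on several points.

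- A reader might infer that most hospital-periods cannot supply a form. They can: 3 of 10 pair-periods are too short, and at most 5 under the strictest counting. Likewise, 8 of 10 hospitals without both conditions is the upper end of a range from 6 when the period runs to 31 October, not a fixed figure.
- A reader might infer that the within-hospital comparison is lost altogether. In Section 7.2 the SF-12 line sits in year 1, near the one-year postoperative visit, which suggests a clock from surgery. On that clock every hospital-period has some patients with a form.
- A reader might infer that most patients lack a form on any reading. This follows on the surgery clock, under a constant surgery rate. It does not follow if the clock runs from registration.
- A reader might infer that the quality-of-life comparison cannot be computed. A cross-sectional comparison at 12 months in the multilevel model needs no baseline. Nor would the economic result merely reflect who had a form, because Section 10 plans costs for all included patients and overall survival is an endpoint.
- A precision argument is also tempting. The documents give no utility standard deviation and no QALY gain per resection, so none is made here.

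The choice of utility algorithm may sit in an analysis plan, and its absence is not counted. The collection schedule is a different matter: an analysis plan cannot create a baseline or a value after month 12.

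**Conclusion.** The point holds in a bounded form. The SF-12 schedule does not support the planned QALYs: with at most one value per condition, a horizon of up to three years and discounting after year 1, patient-level QALYs rest on strong assumptions about utility at every other time. This conclusion needs no outside figure.

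The quality-of-life comparison is computable but weak and unbalanced, and how weak depends on a clock that the protocol does not define:

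- From surgery, about 54% of all patients and 67% of those already in follow-up have no eligible date. This assumes a constant surgery rate; the 54% also takes a 28-month study with surgery up to month 25.
- From the start of the period, 3 of 10 pair-periods are too short (up to 5 if exactly 12 months is excluded). 6 to 8 of 10 hospitals cannot supply both conditions if the period runs to 31 October 2012. An end on 1 October with exact 12s excluded is the extreme case, in which none can.

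The primary endpoint and the cost per additional curative metastasectomy are unaffected. The change should be made, but the main analysis does not depend on it.

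**What to change.** - State the origin of the 12 months in Sections 7.1 and 7.2.
- Give the SF-12 to every patient at his or her own inclusion, and then on common calendar dates in all hospitals, independent of the switch. Place the dates just before or between switch dates. As an example, December 2010, June 2011, December 2011 and June 2012 would give every pair at least one calendar form in each condition.
- Compute QALYs as the area under the utility curve, with death set to 0.
- Analyse quality of life in the stepped-wedge multilevel model with adjustment for the patient's own inclusion score. A common July 2010 score would not exist for patients who enter later.
- If no forms can be added, withdraw the cost-utility analysis and report only the cost per additional curative metastasectomy, which Section 10 already plans.

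The cost is a few extra 12-item forms per patient, some respondent burden and a small amendment. Intervention patients already receive result letters that could carry the form. Section 7.1 describes no such letters in the control period, so control patients would need a separate mailing.

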**2. INTRODUCTION AND RATIONALE**

*2.1 Introduction / background*

The incidence of metachronous metastases after curative colon and rectum resections is approximately 30-50%, with an increasing incidence dependent on the initial stage. Predominant sites of first recurrence in the population with recurrent disease are the liver (± 40%), lung (± 30%) and local recurrence (± 25%) (Kobayashi). These types of recurrent disease can be eligible for curative resection, which is now feasible in an estimated 10-30%. The increase in survival after metastasectomy for resectable recurrent disease is high, with a 5 year overall survival after metastasectomy of approximately 30% for all three types of recurrent disease (Goldberg, Bentrem, Pfannschmidt). It is predominantly dependent on achievement of a R0 resection and the number of metastases, the last probably corresponding to tumor behaviour.

*2.2. Follow-up*

After curative treatment of colorectal cancer, patient surveillance is recommended to detect curable recurrent disease or new primary tumors in an early phase. There was a statistically significant increase in feasibility of intended curative resection of recurrent disease in 5 prospective randomised studies and in the 5 year overall survival in 4 of the 5 studies. Based on the literature, both the Dutch guideline (CBO 2008), the Canadian guideline and the US guideline (ASCO 2005) propose a high intensity program of regular office visits, imaging studies (CBO: liver ultrasound, Canada: liver imaging, ASCO: Computed Tomography (CT) chest-abdomen) and CarcinoEmbryonicAntigen (CEA) tests. Imaging is advised since not all recurrences are detected with an early CEA raise. The value of physical examination in detecting recurrent disease is low (Borie, Sugarbaker).

*2.3. Carcinoembryonic antigen (CEA)*

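### The planned cost per QALY has a horizon of at most 3 years and no extrapolation, so it leaves out most of the survival gain that extra metastasectomies are meant to bring

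*Protocol*

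**What the plan says.** Section 10 plans two economic results. The first is the cost per additional patient who has a curative metastasectomy. The second, introduced as an addition, is a cost per QALY. Together they are to show how costs balance against health, survival and quality of life.

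The horizon is fixed in two sentences: "Costs will be studied from a societal perspective, during a time period maximally 3 years", and "Since the time horizon of the study exceeds one year, both costs and effects beyond the first year will be discounted". The basis is observed data: "Bootstrapping will be performed on the cost and effect pairs in order to calculate confidence intervals". No decision model, survival extrapolation or longer horizon is mentioned. The cost list ends with "additional diagnostic tests, outpatient visits, hospital admissions and travel expenses", so surgery enters through admissions.

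Section 2.1 puts the benefit of resecting recurrent disease on a longer scale, "with a 5 year overall survival after metastasectomy of approximately 30% for all three types of recurrent disease". Section 8.1.1 counts the main endpoint "in the study period: July 2010 – October 2012". Section 5 starts the first pair of hospitals on 1 January 2011, and "the last two hospitals start with the intensified follow-up scheme at January 1st, 2012".

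**The concern.** The mechanism in this trial is earlier detection, then more curative resections, then longer life. The costs of that chain (CEA tests, CT scans, admissions) arise at or before resection. The life-years arise afterwards, over five years and more. An analysis that closes within 3 years records the first and little of the second.

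The protocol's stated objective is a recommendation on cost-effective follow-up for all hospitals. A cost per QALY and an acceptability curve built on a small fraction of the effect could count against a strategy that works as intended. The primary clinical endpoint is not affected.

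**Working it through.** **The plan's own figures.** Section 10 gives no computed economic figure to reproduce, only the 3-year maximum. The sample-size steps in Section 6.4 supply the number of extra resections: 115/0.25 = 460 per group, and 460 × 1.71 = 787, stated as about 800. With 25% recurrence and resection rising from 10% to 25%, the extra resections are 0.25 × (0.25 − 0.10) = 3.75% of patients, or 0.0375 × 800 = 30 per 800.

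**Observation time.** Hospitals switch in pairs every three months (Summary), from January 2011 to January 2012 (Section 5). Counted from 1 July 2010, the switches fall at months 6, 9, 12, 15 and 18. To 1 October 2012 (month 27) this leaves 21, 18, 15, 12 and 9 months on the intervention. These are calendar windows per hospital. A recurrence found part-way through a window has less time left for observation after resection.

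**Survival inputs.**
- Resected: 30% at five years (Section 2.1), so the hazard is −ln(0.30)/5 = 0.2408 per year.
- Not resected: not given in the protocol. Assumed 5% to 10% at five years, so the hazard is −ln(0.05)/5 = 0.5991 or −ln(0.10)/5 = 0.4605 per year.
- Survival is assumed exponential, and each extra resection is assumed to move a patient from the second curve to the first.

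**Formula.** Mean life-years lived within t years of resection are (1 − e^(−λt))/λ. The gain is the resected minus the unresected value, and the share captured is the gain at t divided by the gain at 20 years.

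Example at t = 3: resected (1 − e^(−0.722))/0.2408 = 2.136; unresected at 5%, (1 − e^(−1.797))/0.5991 = 1.392; gain 0.744. At 20 years: 4.119 − 1.669 = 2.450. Share: 0.744/2.450 = 30%.

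| Time observed after resection | Gain, 5% unresected | Share of 20-year gain | Gain, 10% unresected | Share of 20-year gain |
|---|---|---|---|---|
| 9 months | 0.082 | 3.3% | 0.052 | 2.7% |
| 21 months | 0.344 | 14% | 0.227 | 12% |
| 3 years | 0.744 | 30% | 0.510 | 26% |
| 5 years | 1.322 | 54% | 0.953 | 49% |
| 20 years | 2.450 | 100% | 1.948 | 100% |

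The 9- and 21-month rows use the shortest and longest hospital windows, as if resection came on the first day. The 3-year row is the most that the stated maximum could allow. The omitted share therefore runs from about 70% (100 − 30) to about 97% (100 − 3).

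**Sensitivity.**
- Discounting at 4% raises the captured shares to about 3-4%, 14-17% and 31-35% for 9 months, 21 months and 3 years.
- Let 20% of resected patients be cured, with the curve still passing through 30% at five years, a 15-year cap and an unresected median survival of 1 to 2 years. The captured shares are then 2.3% down to 0.2%, 9.5% down to 1.6%, and 20% down to 5%.

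In neither check does the horizon capture much more than a third of the gain.

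**The case against.** The protocol states its horizon openly, and the sentence with the 3-year limit speaks of costs only. That QALYs share it is inferred from the discounting sentence, the bootstrap of observed pairs and the 3-year study duration. The July 2010 to October 2012 period belongs to the metastasectomy endpoint, and the survival endpoints carry no stated cut-off. This is fair, but nothing in Section 10 points to a longer horizon for effects, and the full 3-year case still loses about 70%.

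The lead economic result is the cost per additional curative resection, which is much less exposed to the horizon. This stands, and it limits the importance of the point.

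The cost side is not clear-cut. Metastasectomy is charged only through admissions, and the Summary describes the cost outcome as related to diagnostics. Unresected patients are referred for palliative treatment (Section 7.2.1), which may offset some of the cost. This also stands. The firm part is that QALYs are understated; the direction of the net bias is likely rather than certain.

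A reader might also infer that unequal time under the two schedules distorts the comparison: hospital windows average 12 months on control and 15 on intervention, and at an assumed utility of 0.8 the extra 0.25 year is 0.20 QALY. The document does not support that. It nowhere says that unstandardised totals will be compared, and adjustment for observed time can be left to an analysis plan. With rolling entry, hospital windows are also not per-patient exposures.

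**Conclusion.** The point holds for the horizon. As written, the cost per QALY would omit roughly 70-97% of the undiscounted 20-year survival gain from about 30 extra resections per 800 patients, and is likely biased against the intervention. The range rests on exponential survival, an assumed 5-10% five-year survival without resection, and 9 months to 3 years of observation after resection.

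A reader might take the 3% figure as the share the analysis will capture. It is the low end only: the protocol fixes no observation time after resection, and the share is ten times larger if 3 full years are observed. Nor does the document support the view that a within-trial QALY result must be removed. Such a result is legitimate if it is presented as short-term.

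**What to change.** In Section 10:

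1. Keep cost per additional patient with a curative resection as the lead within-trial economic result.
2. Label any within-trial cost per QALY as short-term, and state that it is not a basis for the cost-effectiveness recommendation.
3. Add a cost per QALY extrapolated to at least five years, preferably lifetime; under the exponential assumption five years still captures only 49-54% of the gain. Apply post-recurrence survival by resection status to the trial's resection proportions, use the discount rates already stated, and vary the survival inputs in sensitivity analysis.

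The cost is a change of wording and a simple model. The downside is that the extrapolated result depends on survival assumptions, including survival without resection, which must be sourced and stated. Recruitment, randomisation and patient care are unchanged.

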Costs of productivity losses will not be taken into account, since the target population largely consists of retired people. Unit costs will be valued using Dutch standard prices. In case no standard prices are available, costs will be calculated according to the Dutch guidelines for cost studies (CVZ) . Volumes on cost categories will be registered on a patient level, except for travelling expenses, for which a question will be added to the Quality of Life questionnaire.

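### As written, the economic bootstrap takes no account of the ten randomised hospitals, so cost-effectiveness intervals and acceptability curves would be too certain, by an amount that depends on an ICC the protocol does not give

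*Protocol*

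**What the plan says.** Protocol section 5 sets the design: "The study is constructed with the stepped-wedge design. This implies a randomization at hospital level". Ten hospitals switch in pairs, the first pair on 1 January 2011 and the last on 1 January 2012. All included patients change schedule with their hospital. Section 7.1 accepts that usual care may differ between hospitals. Section 6.4 multiplies the sample size by 1.71, for a hospital SD of 0.1.

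Section 10 analyses resected metastases "using a multilevel model to adjust for the clustering", and then adds: "For the quality of life data the same analysis will be applied". The economic evaluation uses related effects, namely patients with curative metastasectomy and QALYs. Its statement on uncertainty is "Bootstrapping will be performed on the cost and effect pairs in order to calculate confidence intervals", followed by "Cost effectiveness acceptability curves will be constructed to illustrate the probability that the different follow-up strategies will be cost-effective". On the data it says: "Volumes on cost categories will be registered on a patient level, except for travelling expenses".

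On perspective, section 10 says "Costs will be studied from a societal perspective, during a time period maximally 3 years" and later "Costs of productivity losses will not be taken into account, since the target population largely consists of retired people".

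**The concern.** The clustering adjustment is stated for the clinical outcome and explicitly extended to quality of life, but not to costs or to the cost-effect pairs. Cost volumes are recorded per patient, so the ordinary reading of a pair is one patient's cost and effect. Resampling such pairs without regard to hospital treats patients in one hospital as independent. Each hospital supplies a different share of control and intervention time, so differences between hospitals do not cancel from the comparison.

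A patient present before and after the switch has costs under both schedules. The text does not say whether that patient is one pair or two.

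A cost-effective recommendation is part of the study's stated aim (sections 1 and 3). An acceptability curve that is too steep would overstate how sure that recommendation is. The effect side of the ratio could also carry a tighter interval than the trial's own multilevel analysis of a related outcome.

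**Working it through.** **The plan's own figures.** Section 6.4 compares 10% with 25% at 5% significance and 80% power. The two-sided formula with continuity correction gives 113 per group (115 stated). Then 115/0.25 = 460, and 460 x 1.71 = 786.6 (about 800 stated). One reading that matches the factor of 1.71 is:
- mean binomial variance (0.09 + 0.1875)/2 = 0.13875;
- ICC = 0.01/(0.01 + 0.13875) = 0.067;
- 115/10 = 11.5 patients with metastases per hospital;
- 1 + 10.5 x 0.067 = 1.71.

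The economic evaluation states no figure to reproduce.

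**Hospital weights.** Section 8.1.1 gives July 2010 to October 2012, taken as 27 months. Switches fall at s = 6, 9, 12, 15 and 18 months, two hospitals each (the three-month step is in section 1). Control time totals 2 x (6+9+12+15+18) = 120 hospital-months, and intervention time 270 - 120 = 150. With equal hospital sizes, a hospital's weight in the difference is (27 - s)/150 - s/120, which gives +0.09, +0.045, 0, -0.045 and -0.09. The sum of squares over ten hospitals is 4 x 0.0081 + 4 x 0.002025 = 0.0405.

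**Variance understated.** Set the total variance to 1 and assume 800 independent patients per group.
- A bootstrap that ignores hospital estimates 2/800 = 0.0025.
- The true variance is ICC x 0.0405 + (1 - ICC) x 0.0025.
- The ratio is 1 + 15.2 x ICC.
- Coverage is 2Φ(1.96/√ratio) - 1.
- The chance that the acceptability curve exceeds 95% when true net benefit is zero is 1 - Φ(1.645/√ratio), nominally 5%.

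| Assumed ICC | Variance ratio | SE ratio | Coverage of 95% interval | Curve above 95% |
|---|---|---|---|---|
| 0.01 | 1.15 | 1.07 | 93.2% | 6% |
| 0.02 | 1.30 | 1.14 | 91.4% | 7% |
| 0.05 | 1.76 | 1.33 | 86.0% | 11% |
| 0.10 | 2.52 | 1.59 | 78.3% | 15% |

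Splitting 1,600 patients in proportion to hospital-time (889 and 711) instead gives ratios of 1.15, 1.30, 1.75 and 2.50; coverage at ICC 0.10 is then 78.5%.

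**What the plan's SD of 0.1 implies.** It applies to the resection percentage among patients with metastases.
- On that denominator, 800 x 25% = 200 per group. The naive variance is 2/200 = 0.01 and the ratio is 1 + 3.05 x 0.067 = 1.20. The SE ratio is 1.10 and coverage about 92.6%.
- Among all patients the rates are 2.5% and 6.25%. If recurrence is constant at 25%, the hospital SD is 0.025. The mean variance is (0.0244 + 0.0586)/2 = 0.0415, so ICC = 0.000625/(0.000625 + 0.0415) = 0.015. The SE ratio is 1.11 and coverage about 92.3%.

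**Calendar time.** Number the nine quarters 0 to 8. The mean control quarter is 70/40 = 1.75 and the mean intervention quarter 290/50 = 5.80. The gap is 4.05 quarters, or 12.15 months. An assumed drift of 0.02 SD per quarter, used only for illustration, shifts the difference by 0.081 SD. That is about 1.6 naive standard errors, and coverage falls to about 64% even at ICC 0.

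**The case against.** The strongest reply is that the protocol is silent here rather than wrong. It names no resampling unit and nowhere says that patients are treated as independent. Bootstrapping pairs is compatible with resampling whole hospitals, and an analysis plan that is not shown may say so. This stands against any claim that the plan has chosen to ignore hospitals. It does not remove the point: section 10 extends the clustering adjustment to quality of life by name, leaves the economic evaluation with a plain bootstrap, and registers costs per patient.

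On size, a reader might apply the ICC of 0.067 to 800 patients per group and infer an SE ratio of 1.42 and coverage of 83%. The documents do not support that, because this ICC belongs to patients with metastases, of whom about 200 per group are expected. Taking √1.71 = 1.31 as the understatement (87% coverage) likewise carries a factor set for the resection outcome over to costs.

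The calculation also treats the two groups as different people. Positive correlation within patients who cross over would lower the true variance of the difference, and hospital effects would cancel more fully than the time weights imply. This stands as a limit on the figures.

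A reader might also count the missing calendar term as a cause of narrow intervals. It is a source of bias, and the clinical model in section 10 names no time term either, so it is not peculiar to the bootstrap.

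Finally, the exclusion of productivity losses is stated openly with a reason, and travel expenses are included. The societal label is therefore a disclosed scope choice. It has no bearing on interval width.

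**Conclusion.** The point holds as a gap between the stated economic method and the design. Followed as written, the bootstrap does not carry the hospital clustering that section 10 adjusts for elsewhere, and it leaves the pair undefined for patients who contribute to both periods. Intervals and acceptability curves would then be too certain.

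The amount is not fixed by the documents. It is small at an ICC of 0.01 and material at 0.05 and above. The only hospital variation that the plan quantifies, for a different outcome, points to the small end. All the coverage figures rest on equal hospital sizes, independent patients and the stated switch dates.

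The calendar gap of about 12 months is a separate risk of bias, whose size depends on a cost trend that the documents do not give. The primary clinical comparison is not affected by the bootstrap. The perspective label is a minor wording matter.

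**What to change.** In section 10, replace the plain bootstrap with one of two methods:
- a two-stage bootstrap that draws hospitals within switching sequence, then patients with all their periods kept together; or
- a bivariate multilevel model for cost and effect, with hospital and calendar-period terms written out. They cannot be borrowed from the clinical model, which names no period term.

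Either way, define the cost-effect pair for patients who cross over. If the bootstrap is chosen, re-estimate the increments with a calendar-period adjustment in each resample, because resampling hospitals alone does not remove a time trend. Add a caution that ten hospitals, two per sequence, are few for any cluster-level method.

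As a secondary edit, describe the perspective as health-care plus travel costs, or add productivity losses for patients of working age as a scenario.

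The cost is a few sentences of protocol text, some programming, and intervals that will probably be wider. Apart from the optional productivity scenario, no new data are needed.
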